## Abstract

**Background:**

Teenagers and young adults with type 1 diabetes (T1D) experience significant burden managing this serious chronic condition and glycaemic control is at its unhealthiest during this life stage. Flash glucose monitoring (FGM) is a new technology that reduces the burden of glucose monitoring by easily and discreetly displaying glucose information when an interstitial glucose sensor worn on the upper arm is scanned with a handheld reader, as opposed to traditional capillary glucose sampling by finger prick (otherwise known as self-monitored blood glucose, SMBG). The effectiveness of this technology and impacts of its long-term use in youth with pre-existing suboptimal glycaemic control are unknown. This study therefore aims to investigate the effectiveness of FGM in addition to standard care in young people with T1D.

**Methods:**

This is a two phase study programme including a multi-centre randomised, parallel-group study consisting of a 6-month comparison between SMBG and FGM, with an additional 6-month continuation phase. We will enrol adolescents with T1D aged 13–20 years (inclusive), with suboptimal glycaemic control (mean glycated haemoglobin (HbA1c) in past 6 months ≥75 mmol/mol [≥9%]). Participants will be randomly allocated (1:1) to FGM (FreeStyle Libre; intervention group) or to continue SMBG with capillary blood glucose testing (usual care group). All participants will continue other aspects of standard care with the study only providing the FreeStyle Libre. At 6 months, the control group will cross over to the intervention. The primary outcome is the between group difference in changes in HbA1c at 6 months. Additional outcomes include a range of psychosocial and health economic measures as well as FGM acceptability.

**Discussion:**

>If improvements are found, this will further encourage steps towards integrating FGM into regular diabetes care for youth with unhealthy glycaemic control, with the expectation it will reduce daily diabetes management burden and improve short- and long-term health outcomes in this high-risk group.

**Trial registration:**

This trial was registered with the Australian New Zealand Clinical Trials Registry on 5 March 2018 (ACTRN12618000320257p) and the World Health Organization International Clinical Trials Registry Platform (Universal Trial Number U1111-1205-5784).

## Background

Type 1 diabetes (T1D) is a serious chronic metabolic disorder often diagnosed during childhood and is characterised by high blood glucose levels resulting from pancreatic β-cell destruction [1]. Recently, the International Diabetes Federation estimated 500,000 children aged 14 years and younger had type 1 diabetes worldwide [2]. Increasing incidence [3–6] and prevalence [4, 6, 7] of T1D among youth has been observed in several countries. Complications of T1D include potentially life-threatening episodes of diabetic ketoacidosis (DKA) and severe hypoglycaemia, micro- and macrovascular diabetes-specific complications, and poorer mental health among children and adolescents with diabetes compared to those without diabetes [8]. There is no cure for T1D, therefore the goal of treatment is to achieve and maintain optimal glucose levels, particularly through insulin therapy, physical activity and diet [9].

Up until now, frequent daily self-monitored blood glucose (SMBG) testing has been essential for monitoring blood glucose levels, safety, and informing treatment decisions [10]. The evidence for the benefits of self-monitoring glucose levels on glycaemic control is well established [11, 12], with an association with lower glycated haemoglobin (HbA1c; the current standard measure of glycaemic control) by 0.5% for each additional SMBG check per day, up to 5 checks/day (*p* < 0.001) seen in an observational study of 20,555 children and adults with T1D [11]. Finger pricking (capillary glucose testing) is the most common approach to SMBG. However, pain, inconvenience, fear of stigmatization and embarrassment are common barriers to SMBG adherence among adolescents [13–17].

### Type 1 diabetes during adolescence

Adolescence is a high-risk period where glycaemic control is at its worst [18], treatment adherence is a particular challenge [19] and the strain of self-management takes a toll on adolescents’ and their parents’ quality of life [20]. Type 1 diabetes exchange data indicate only a minority of young people meet international guidelines for glycaemic control (HbA1c < 58 mmol/mol [< 7.5%]) [21]. During this life stage, barriers to treatment adherence include the major physical and cognitive changes and increasing independence regarding eating behaviour, physical activity and other aspects of lifestyle, such as sleep, increase the burden of managing T1D [22]. Most adolescents with T1D do not adhere to SMBG recommendations [19], with some adolescents undertaking SMBG only when experiencing symptoms of low or high blood glucose levels. Frequent misreporting and fabrication of SMBG data has also been described [23, 24].

### Flash glucose monitoring

Flash glucose monitoring (FGM) technology, sometimes referred to as intermittent continuous glucose monitoring (iCGM), is an accurate, safe, and acceptable approach to monitoring interstitial glucose levels in children (≥4 years) and adults [25–27]. FGM provides an up-to-date interstitial glucose level, a graph of retrospective data and predicted glucose trend when the user scans the sensor with a handheld receiver [26]. These interstitial glucose measurements have been found to be accurate compared with capillary blood glucose reference values [26]. Higher rates of scanning are associated with indicators of better glycaemic control, such as increased time in range (defined as glucose levels between 3.9 and 10.0 mmol/L [70–180 mg/dL]), reduced time in hyperglycaemia (> 10 mmol/L [> 180 mg/dL]), and improved HbA1c [28, 29]. FGM is less expensive than a similar technology, traditional continuous glucose monitoring (CGM), and does not require regular calibration, like the majority of current CGM systems. However, FGM is retrospective, and therefore does not have the CGM feature of automatic alerts in response to pre-defined low or high glucose levels. Adverse events associated with FGM use are typically limited to skin issues associated with sensor insertion and reactions to sensor adhesive [18, 25, 27, 30].

Evidence of the potential to increase glucose monitoring among adolescents by using FGM technology is emerging [29–32]. FGM may provide an important opportunity to engage adolescents in their diabetes care by reducing their disease burden and facilitating access to glucose data more frequently, which in turns enables adolescents to make better informed management decisions. The easy instant access to glucose levels that FGM affords is particularly suited for young people where motivation is lacking and the burden of disease is high [33]. However, to our knowledge, there is no evidence demonstrating the superiority of FGM over SMBG for improving clinical outcomes in this challenging patient population. A 6-month randomized controlled trial evaluating FGM among adults with well controlled T1D reported reduced time in hypoglycaemia in the intervention group compared to the SMBG group, but no significant change in HbA1c [31]. Short-term improvements in glycaemic outcomes, including time in range and reduced time in hyperglycaemia, as well as improvements in HbA1c, have been observed in a single-arm study among children and teenagers using FGM for 8 weeks [30]. There is evidence of clinically significant improvements in HbA1c (by ≥0.5% in HbA1c) among T1D patients aged 1–25 years being sustained at 12 months [32] in a real-world setting. This finding is similar to some other diabetes technology, with a recent insulin pump study among adolescents with unhealthy glycaemic control showing sustained improvements in HbA1c from baseline out to 12 months [34]. The same study reported short-term improvements in diabetes-specific and generic health- related quality of life (HRQoL) related to insulin pump use that were not sustained [34]. Research is clearly warranted to investigate the effectiveness of FGM on glycaemic control among young people, particularly those with the unhealthiest glycaemic control (who are usually excluded from manufacturer-funded studies and are plausibly the group with the greatest potential to benefit if FGM is effective). Broader impacts of FGM on salient outcomes such as fear of hypoglycaemia, diabetes treatment satisfaction, and HRQoL also warrant investigation.

### Aim, objectives and hypotheses

The overall study aim is to evaluate, in a randomised controlled trial, the clinical effectiveness of FGM compared to SMBG for adolescents with T1D and a history of suboptimal glycaemic control. The primary objective is to investigate the effectiveness of FGM compared to SMBG in reducing HbA1c (i.e., the primary analysis will be on a modified intention to treat basis, using all available data).

The secondary objectives are to investigate:the effectiveness of FGM compared to SMBG in increasing glucose monitoring behaviour during the 6-month trial period;the effectiveness of FGM compared to SMBG in changing disease specific and generic HRQoL, fear of hypoglycaemia, and treatment satisfaction during the 6-month trial period;acceptability and feasibility of using FGM to self-monitor glucose levels during the 6-month trial period; andAdverse events (e.g. skin problems, diabetic ketoacidosis, severe hypoglycaemia) during the 6-month trial period.

The tertiary objectives are to explore:all of the primary and secondary analyses using participants from the FGM group who scanned at least once per day 12 days out of 14 in the two weeks prior to the 6 month study visit (which is a definition modified from a recent landmark CGM study [35]) and excluding any participants from the SMBG group who used FGM at any time during the study (i.e., a per protocol analysis with potential confounding by characteristics associated with compliance, although all participants in the study have a recent history of suboptimal glycaemic control and so are likely to have similarly low baseline rates of SMB testing)the impact of FGM compared to SMBG on sleep and physical activity during the 6-month trial period; andall study outcomes in both groups at 12 months, including estimating within-group changes in the FGM group from 6 months to 12 months (to investigate persistence of changes) and within-group changes in the crossed over group from 6 months to 12 months (to see if any such changes are consistent with those in the FGM group from baseline to 6 months).

It is hypothesized that compared to SMBG, FGM will result in a clinically relevant (at least 1.0%; 10 mmol/mol) and statistically significant reduction in mean HbA1c at 6 months’ post-baseline. Additionally, it is hypothesized that there will be statistically significant improvements in other important outcome measures in health, wellbeing, and diabetes management in the FGM intervention group at 6 months, compared to the SMBG group.

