#### Flash glucose monitoring

All data will be downloaded at every follow-up visit and exported from the FGM reader using the FreeStyle Libre computer software version 1.0 (Abbott Diabetes Care, Ltd., Witney, Oxon, UK). Individual glucose measures, mean interstitial glucose level, and frequency of scans in the previous two weeks will be recorded.

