The main analyses will follow a modified intention- to-treat principle with all participants analysed in the group to which they were randomised, regardless of actual sensor wear. Per protocol analyses will be also be investigated by including only those from the FGM group who scanned at least 12 out of 14 days in the two weeks prior to the 6-month study visit and excluding any participants from the SMBG group who used FGM at any time during the study. All models will include variables used in minimization [59].

Any missing HbA1c values will be imputed using multiple imputation with chained eqs. (100 imputations after at least 100 burn-ins) and with the imputation model including: gender, HbA1c status at baseline as well as values of that variable from other time points, insulin regimen, frequency of self-monitored glucose (capillary or interstitial) and socioeconomic status. If missing data exceeds 10%, plausible scenarios involving informative missing data will be investigated to explore the robustness of findings.

Statistical analyses will be performed using R 3.5.2 or Stata 15.1 software (or later versions) with two-sided *p* < 0.05 considered significant. To maintain the integrity of the study, statistical analyses will be performed by the biostatistician blinded to group allocation.

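### The exploratory per-protocol re-run covers glucose-monitoring frequency but selects only the FGM arm on scanning in the outcome fortnight, so it can show a spurious increase in monitoring

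*Protocol article*

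**What the plan says.** All references are to the protocol article.

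- **Scope of the re-run.** Under Aim, objectives and hypotheses, the tertiary objectives repeat "all of the primary and secondary analyses using participants from the FGM group who scanned at least once per day 12 days out of 14". No secondary outcome is exempted.
- **Rule for the FGM arm.** Participants are kept if they "scanned at least once per day 12 days out of 14 in the two weeks prior to the 6 month study visit". The Statistical analysis section repeats the rule for those "who scanned at least 12 out of 14 days in the two weeks prior to the 6-month study visit".
- **Rule for the SMBG arm.** The only restriction is "excluding any participants from the SMBG group who used FGM at any time during the study". There is no minimum number of capillary tests.
- **The outcome concerned.** The first secondary objective is "the effectiveness of FGM compared to SMBG in increasing glucose monitoring behaviour during the 6-month trial period".
- **How it is measured.** For FGM, under Glucose monitoring behaviour, the "frequency of scans in the previous two weeks will be recorded". For SMBG, the number of meter tests is taken over the same length of time. The planned comparison is Poisson regression, or negative binomial if the counts are over-dispersed.
- **Stated caveat.** The tertiary objective concedes possible confounding by characteristics linked to compliance. It then offers the reassurance that recent poor control makes low baseline testing likely in all participants.

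**The concern.** At 6 months, the rule that admits an FGM participant and the outcome on which that participant is compared come from the same behaviour in the same 14 days. The rule counts days with a scan and the outcome counts scans, so the rule is a close component of the outcome. It removes low counts from one arm only.

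The two arms then differ in their count distributions even if FGM changes nothing. This is distinct from ordinary complier confounding, in which people who adhere also differ in other ways that affect, for example, HbA1c. At stake is whether the per-protocol result for this one outcome can be interpreted.

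**Working it through.** **Inputs from the protocol.** 32 participants per arm (Sample size); the 12-of-14-day rule; a 14-day outcome window; two-sided 5% level. The plan states no figure on this point, so there is none to reproduce.

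**Inputs assumed.** The protocol gives no monitoring rates. The range used is a mean of 1 to 6 checks a day, a between-person coefficient of variation (CV) of 0 to 0.8, and a within-person log-SD between occasions of 0.3 or 0.6.

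**Step 1: the floor.** A retained FGM participant has at least 12 scans in the window, or 12/14 = 0.86 a day. The SMBG arm has no floor.

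**Step 2: a hand calculation with no differences between people.** Let everyone check at exactly 2 a day, with Poisson daily counts.

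- Chance of at least one check on a day: 1 - exp(-2) = 0.865.
- Chance of 12, 13 or 14 such days out of 14 (binomial): 0.291 + 0.286 + 0.131 = 0.708.
- Mean number of such days among those retained: (12 × 0.291 + 13 × 0.286 + 14 × 0.131)/0.708 = 12.77.
- Mean checks on such a day: 2/0.865 = 2.313.
- Mean in the retained arm: 12.77 × 2.313/14 = 2.11 a day, against 2.00 in the other arm.

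The ratio is about 1.05 from selection on chance alone. It grows once people, or occasions within a person, vary.

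**Step 3: simulation under no effect.** Both arms had identical distributions at baseline and 6 months, and the rule was applied to the FGM arm only. The test was a regression of log(count + 1) on arm and log baseline count, with robust (HC3) standard errors and 1,500 runs per scenario. Each row gives the range over five combinations of between-person and within-person variation.

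| Mean checks/day | FGM arm retained | Spurious FGM:SMBG ratio | False positives, per protocol | False positives, as randomised |
|---|---|---|---|---|
| 1 | 11-19% | 1.57-2.58 | 54-98% | 3.7-5.2% |
| 2 | 41-62% | 1.19-1.85 | 37-85% | 4.1-6.4% |
| 3 | 55-89% | 1.06-1.60 | 10-57% | 4.2-5.2% |
| 4 | 65-97% | 1.02-1.43 | 4-39% | 3.5-5.7% |
| 6 | 76-100% | 1.00-1.29 | 4-23% | 3.5-5.3% |

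The first row uses only runs with at least 4 FGM participants retained.

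**Step 4: does similar baseline testing help?** With the same underlying mean for everyone (CV 0, log-SD 0.3) at 2 a day, the ratio is 1.19 and the false-positive rate 48%. It does not remove the bias. Across the table, low rates make the bias larger, because the rule then discards more people.

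**Step 5: what drives it?** Applying the same rule to both arms gives ratios of 0.99-1.01 and 2.5-5.0% false positives. The one-sidedness produces the inflation.

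**Step 6: closeness to the planned model.** The regression in step 3 stands in for the planned count model. An over-dispersed Poisson regression gave the same direction (adjusted ratio 1.16-1.53 at 2 a day). In some scenarios that check also rejected above 5% as randomised (up to 11.5%), so it supports the direction and not the exact rates.

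**The case against.** The strongest case on the other side has four parts.

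- **The analysis is exploratory.** The per-protocol re-run is a tertiary objective, and the main analyses keep everyone in the group to which they were randomised. This stands, and it limits the point to a minor one.
- **The protocol already warns about compliance.** It does, but in terms of the kind of person who complies. Steps 2 and 4 show bias with no such differences, so the warning does not reach this problem.
- **The windows coincide only at 6 months.** This is correct. The 3-month count comes from a different fortnight, although from the same selected people, and the objective spans the whole 6-month period.
- **The size rests on assumed rates.** This is also correct. Where 97% or more of the FGM arm meets the rule, the simulated false-positive rate is 3.5-5.3%, which is nominal. Heavy loss from the FGM arm would also be visible in a per-protocol table.

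A reader might infer that no complier rule could give a valid test, since the outcome is built into the selection. Step 5 contradicts this: a rule applied to both arms restores near-nominal error under the simulated null. Such a comparison would still condition on behaviour after randomisation, and the protocol does not plan it.

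A reader might also infer that the result will be presented as evidence that FGM increases monitoring. No section says so.

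**Conclusion.** The point holds in a limited form. As written, the per-protocol re-run of monitoring frequency selects one arm on a close component of the outcome, in the same fortnight at 6 months, and can show an increase when there is none.

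The size depends on monitoring rates that the documents do not give. It is large at the low rates the protocol itself expects and fades to nothing when nearly all FGM participants qualify. The figures assume no true effect, identical distributions in the two arms, Poisson daily counts, and a log-count regression in place of the planned count model.

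It would be wrong to extend this to the trial's main results. The primary HbA1c analysis and the as-randomised analysis of monitoring do not use the selection. Severity is minor: one exploratory re-analysis of one secondary outcome.

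**What to change.** In the tertiary objectives and in the per-protocol sentence of the Statistical analysis section, exclude glucose-monitoring frequency from the per-protocol re-run. State that this outcome is analysed only in the groups as randomised. For the FGM arm, report the proportion meeting the 12-of-14-day rule as a descriptive measure of adherence.

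The cost is a wording change in two places. It needs no new data or participants, and the only loss is an exploratory comparison that could not be interpreted.

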## Methods

### Study design

Managing Diabetes is a ‘Flash’ is a two phase study programme consisting of a multi-centre randomised, parallel-group study consisting of a 6-month comparison between SMBG and FGM, including a 6-month continuation phase (see Fig. 1). Once enrolled, the total study period is 12 months for each participant (12 months of FGM for the intervention group will enable an investigation of sustained FGM outcomes). During the continuation phase, the FGM group will continue the intervention for a further 6 months and the control group will cross over and receive a 6-month FGM intervention. The primary purpose of offering FGM to the control group at 6 months is to encourage retention and engagement.

**Fig. 1 Fig1:**
[figure not shown]
CONSORT flow diagram

Scientific peer review was undertaken both internally, by the Department of Women’s and Children’s Health, University of Otago, and externally, by the Cure Kids Medical and Scientific Advisory Committee. The Southern Health and Disability Ethics Committee approved this study (17/STH/240). The protocol underwent Māori (indigenous New Zealanders) consultation, which fostered input into this study. All district health boards approved recruitment and conduct of the study at their site. The trial was officially registered with the Australian New Zealand Clinical Trials Registry (ACTRN12618000320257p; http://www.ANZCTR.org.au/ACTRN12618000320257p.aspx) on 5 March 2018 and was issued a Universal Trial Number (U1111–1205-5784) by the World Health Organization International Clinical Trials Registry Platform. The University of Otago is assuming overall responsibility for the initiation and management of the trial (i.e., is the Trial Sponsor). The study is in no way funded or affiliated with the manufacturer of the FGM system under investigation or any manufacturer of a competing system.

### Recruitment

Adolescents with T1D meeting eligibility criteria for age, duration since diabetes diagnosis, and absent CGM/FGM use in the previous 4 months will be invited to participate in the study during routine diabetes clinic visits. The diabetes clinics were selected where an investigator was affiliated with both the University of Otago Medical School and a district health board (New Zealand’s regional organisations responsible for delivering publicly funded healthcare services to both urban and rural patients). Combined, these district health boards (DHBs) serve a population of approximately 1.2 million people [36] and provide care to approximately 619 people aged 13–20 with T1D [37]. It is assumed all patients with diabetes in these catchments would attend these clinics, as minimal private practice in diabetes is provided within New Zealand’s predominantly public health system.

After a potential participant is identified by diabetes clinic staff, they will receive a brief overview of the study and their interest in the study will be ascertained. Patients who are interested in the study will then be pre-screened over the phone by research staff and sent an information sheet, which explains the study objectives and participant responsibilities in full. Research staff will respond to all study-related questions and schedule a screening visit to confirm eligibility. The inclusion and exclusion criteria for assessing eligibility to participate in the study (Table 1) will be used during a screening visit conducted with the potential participant, any accompanying participant support people, family, or whānau (extended family) and research staff. Each centre will pre-screen and refer patients until the target sample size is achieved. Trial investigators will not receive financial or non-financial incentives for enrolment.

**Table 1 Tab1:** Inclusion and exclusion criteria for participation in Managing Diabetes in a ‘Flash’

Inclusion criteria	Exclusion criteria
• Aged 13 to 20 years (inclusive)	• Any severe diabetes related complications (nephropathy on treatment, retinopathy with associated visual loss – milder degrees will not be excluded)
• Mean HbA1c over previous 6 months ≥75 mmol/mol (≥9%)	
• Diagnosed with T1D for at least 12 months	• Other severe uncontrolled medical or psychiatric co-morbidity/severe mental illness
• Prescribed > 0.5 units of insulin/kg/day (with no restrictions based on insulin regimen)	
• Planned to continue with routine clinical care during the initial 6-month RCT	• Currently using a CGM or FGM device or has used one continuously (other than for intermittent hospital use) within the previous 4 months
• Resident in and expecting to remain in regions affiliated with the Canterbury, Capital and Coast, and Southern District Health Boards for the following year	• Participation in another device or drug study that could affect glucose measurements during the study period
	• Pregnant, lactating, or plan to become pregnant
• Ability to understand study procedures, including English language proficiency, and to comply with them for the entire length of the study	
	• Inability of individual (for those aged 16 years and older) or legal guardian (for those aged 13–15 years) to give written informed consent

